### Exploratory analyses

Potential treatment mechanisms (motivation, distress tolerance, emotional and behavioral self-regulation skills, and negative affect) will be examined separately, rather than simultaneously, given our limited sample size and ability to tease apart the relative contributions of related variables. Mediation analyses will be temporally ordered, such that mediators are assessed after the intervention (controlling for baseline levels of mediators), and outcomes will be assessed at a later time point than the mediators (controlling for baseline levels of outcomes). Though power will be limited, these analyses will at least inform us whether the hypothesized mediators are (a) likely to be influenced by treatment and (b) are likely to associate with our primary outcomes. Conducting these analyses will also provide information to plan a future, larger-scale trial.

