### Stage 1B

Stage 1B will employ a randomized controlled trial design to pilot test iCOPE relative to the TAU control condition (see description of treatment conditions below). Adult patients (*N *= 80) meeting eligibility criteria will be randomly assigned to either the iCOPE or TAU conditions.

Following the initial evaluation, in which patients are admitted to buprenorphine treatment, staff will refer potentially eligible patients to study personnel. Interested participants will meet with study personnel in a private setting at the clinic. Informed consent will be obtained, and final eligibility will be determined. Eligible participants will complete a baseline assessment, including two brief behavioral measures of DT (Mirror Tracing and Breath Holding; see Assessments). Participants will then be randomly assigned to iCOPE or TAU. Participants in the iCOPE condition will complete the brief computerized intervention. They will also be informed about the text message element of the intervention and instructed in these procedures. We will recruit 80 participants who will be assigned to condition at a 3:1 ratio, with 60 participants assigned to iCOPE and 20 participants assigned to TAU. Participants will be scheduled to return to the clinic for follow-up appointments consisting of an online survey, behavioral DT measures, and urine collection. Follow-ups will occur at 1-, 4-, 8- and 12-weeks post-treatment initiation.

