## Intervention conditions

### iCOPE

iCOPE will involve two delivery modes: computer and text message (see Fig. 1). The proposed intervention will initially target motivational processes in combination with introductory strategies for managing physical and emotional distress through a single, brief, computer-delivered, session followed by 8 weeks of theoretically-informed text messages intended to enhance motivation and promote DT (see Table 1).

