### Primary outcome

The primary outcome of this study is percentage of days positive for drug use in between assessments (self-report and biochemically verified; see Table 2). The interviewer-delivered Timeline Follow-Back will assess daily opioid use, other illicit substances (e.g., cocaine), and alcohol use. It has demonstrated good reliability [37] and has been validated for the assessment of opioids and other substance use [38]. Urine Toxicology Screens will be administered at all time points to screen for the presence of opioids and other illicit substances.

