## Discussion

The prevalence of OUD has reached epidemic rates in United States, and opioid-involved overdoses are now the country’s leading cause of injury deaths [50]. MOUD, including the use of buprenorphine, is effective at producing significant reductions in illicit opioid use as well as improvements in health-related outcomes (e.g., reduced risk of HIV) [6, 51]. However, despite the many advantages associated with buprenorphine treatment, nearly half of participants are unable to achieve stabilization [7], and many patients lapse or discontinue treatment in the initial weeks [8]. This is notable as early lapses are related to poor treatment prognosis and retention [8, 52]. Given high rates of noncompliance and/or discontinuation, there have been recent calls to find innovative interventions to enhance motivation, adherence, and retention in buprenorphine treatment [53].

Consistent with a negative reinforcement model of substance use, aversive internal states, that occur in the context of early periods of abstinence, may contribute to difficulties with buprenorphine stabilization [54]. Accordingly, an intervention that (a) cultivates motivation for abstinence over and above the reinforcing effects of opioids and (b) teaches adaptive strategies for tolerating physical and psychological discomfort may optimize stabilization on buprenorphine to improve the likelihood of long-term recovery. This Stage 1 behavioral treatment development trial seeks to develop, and pilot test, an innovative digital health intervention that aims to enhance motivation to engage in treatment and increase tolerance of distress to facilitate buprenorphine stabilization by providing skills training and motivational reminders in ‘real-time.’

At the conclusion of this study, our goals are to (1) evaluate the feasibility, acceptability, and preliminary efficacy of the iCOPE intervention components and (2) explore potential mechanisms underlying the effects of the intervention. Results of this study will be used to determine whether to proceed with further testing through a large-scale, fully-powered trial. Even if this study produces null effects of the proposed intervention, the data will still yield valuable information to inform future intervention development efforts.

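### The exploratory mediation models adjust only for baseline, so drug use between intake and the mediator visit can produce a mediator-outcome association that is reverse causation

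*Protocol article*

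**What the plan says.** All references are to the protocol article. Under Exploratory analyses, each candidate mechanism (motivation, distress tolerance, emotional and behavioural self-regulation, negative affect) is examined on its own. The models are ordered in time: "mediators are assessed after the intervention (controlling for baseline levels of mediators"), and then "outcomes will be assessed at a later time point than the mediators (controlling for baseline levels of outcomes"). No other control is named for these models, and no visit is fixed for the mediator or the outcome. The stated purpose is to learn whether the mediators are "likely to be influenced by treatment and (b) are likely to associate with our primary outcomes", and to help plan a larger trial. The only limitation acknowledged there is low power.

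For timing, the iCOPE section describes a brief "computer-delivered, session followed by 8 weeks of theoretically-informed text messages", and Stage 1B states: "Follow-ups will occur at 1-, 4-, 8- and 12-weeks post-treatment initiation". The primary outcome is the "percentage of days positive for drug use in between assessments". Table 2 schedules the Timeline Follow-Back and urine screens at intake and at every follow-up. Use in each interval before a mediator visit is therefore already collected.

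**The concern.** Placing the outcome after the mediator rules out later use as a cause of the mediator. It does not rule out use that came before the mediator visit. On the document's own account that use matters. The Discussion says that "many patients lapse or discontinue treatment in the initial weeks" and that "early lapses are related to poor treatment prognosis and retention". The Background places negative internal states in the context of withdrawal, and the readiness ruler asks about motivation to change opioid use itself, so both could respond to recent use. Use up to the mediator visit is then a plausible common cause of the mediator and of later use, and intake use is only a partial proxy for it.

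At stake is the mediator-outcome link, point (b) of the stated purpose. A measure that merely follows early use could be carried into the next trial as a promising target. The low-power caveat warns of missed links, not of this bias, and a larger trial using the same model would keep it.

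**Working it through.** The documents give no mediation figure, correlation or effect size, so there is nothing to reproduce. From the documents come N = 80, the 60/20 split and the two baseline controls. Everything else below is assumed.

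**Set-up (standardised normal variables, complete data).** Y0, Y1 and Y2 are use at baseline, up to the mediator visit, and afterwards. M0 and M1 are the mediator at baseline and at its visit (higher is better). A is arm.
- Y1 = 0.4·Y0 − d·A + noise. Here d is the effect of iCOPE on early use by some other route.
- M1 = 0.5·M0 − g·Y1 + noise of variance 0.75 − g². Here g is the reverse effect of use on the mediator.
- Y2 = ρ·Y1 + noise. The mediator has no effect on later use.

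**Path b as written** regresses Y2 on M1, A, M0 and Y0. Given those covariates, Y1 has residual variance 1 − 0.4² = 0.84. M1 has residual variance 0.84g² + 0.75 − g² = 0.75 − 0.16g². The spurious coefficient is therefore

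b = −0.84·ρ·g / (0.75 − 0.16g²)

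- g = 0.2, ρ = 0.5: −0.084/0.7436 = −0.113
- g = 0.3, ρ = 0.6: −0.1512/0.7356 = −0.206
- g = 0.4, ρ = 0.7: −0.2352/0.7244 = −0.325

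**Hand check of the middle case.** The residual variance of Y2 is 1 − 0.16·0.36 − 0.206²·0.7356 ≈ 0.911. The standard error of b is about √(0.911/(75·0.7356)) ≈ 0.129, so |b|/SE ≈ 1.60. The false-positive rate is about 1 − Φ(1.99 − 1.60) ≈ 35%.

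**Simulation, 1,500 trials per setting at N = 80, d from 0 to 0.8, two-sided 5% tests:**

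| g, ρ | Path b falsely significant, as written | With Y1 added |
|---|---|---|
| 0, 0.6 | 5.2–5.8% | 5.3–6.0% |
| 0.2, 0.5 | 13.8–14.6% | 4.5–6.1% |
| 0.3, 0.6 | 33.9–36.8% | 4.9–6.1% |
| 0.4, 0.7 | 71.9–73.9% | 4.1–5.4% |

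With Y1 added, the mean path-b coefficient lies between −0.006 and 0.001. A second run over similar assumptions (d = 0.4) gave 18% to 79% as written and 4.4% to 5.6% with Y1.

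**Full indirect effect.** Path a averages g·d. In the middle case with d = 0.5 it is 0.15, against a standard error of about √(0.75·(1/60 + 1/20)) = 0.22, so it is rarely detected. The product is 0.15 × (−0.206) ≈ −0.03 SD. In the simulations with g above 0, its 95% interval excluded zero as follows:
- N = 80, d = 0: about 1% to 4% of trials.
- N = 80, d = 0.3 to 0.8: 0.5% to 20% of trials, above about 5% only in the stronger settings.
- N = 80, Y1 added: at most 1.1% of trials.
- N = 800, d = 0.3 to 0.8, as written: 8% to nearly 100% of trials. The bias does not shrink with sample size.

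**Cost of adjusting.** Suppose the mediator does work, with the same effect b in both intervals. The mediated effect on Y2 is then a·b·(1 + ρ), and the Y1-adjusted model recovers a·b, a share of 1/(1 + ρ). For ρ = 0.7 to 0.5 that is 59% to 67%. A simulation with the effect carried wholly by the mediator gave about 58% to 66%.

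**The case against.** The analysis is labelled exploratory, speaks of association and not causation, and belongs to a pilot that says it has modest expectations of rejecting null hypotheses. A false-positive rate is therefore an imperfect yardstick. The sizes come entirely from assumed correlations in a linear, normal, complete-data model, whereas the outcome is a percentage of days. If use does not move the mediator, there is no inflation. Exact lags are also something an article may leave to a fuller plan. All of this stands, and the absence of named visits is not in itself an error. What remains is that the text does name a control set, and that set omits a variable the document itself gives reason to expect matters.

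A reader might infer three stronger things, and the documents support none of them.
- That reverse causation will show up as a working mechanism. A mechanism needs both paths. If iCOPE does not alter early use, the indirect effect centres on zero, and even otherwise a false one is uncommon at N = 80.
- That the plan claims a causal mediator-outcome link. It does not.
- That only the week-8 mediator with weeks 8–12 use qualifies as following the intervention. The computer session at intake can also be meant, and a week-1 mediator has only one week of use before it.

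The adjustment also has a real drawback. Use up to the mediator visit is post-randomisation, and conditioning on it removes genuine mediation that acted early.

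**Conclusion.** The concern holds for the mediator-outcome path. With only baseline controls, the association the plan wants to learn from can be produced by use before the mediator visit. Under the assumed inputs (g 0.2 to 0.4, ρ 0.5 to 0.7) it was falsely significant in roughly 14% to 79% of trials of 80, against about 5% with the extra covariate. The existence of the bias follows from the model structure whenever use affects the mediator and carries forward. Its size is not known from the documents. Its direction could also differ by mediator: if early abstinence temporarily raises negative affect, as the Discussion's account of aversive states in early abstinence allows, the same omission could hide a real link. The point is confined to the exploratory mechanism aim. The primary, feasibility and acceptability analyses are untouched.

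**What to change.** In Exploratory analyses, name the mediator-outcome pairs, for example:
- week-1 mediator with weeks 1–4 use;
- week-4 mediator with weeks 4–8 use;
- week-8 mediator with weeks 8–12 use.

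For each pair, fit the outcome model twice: with the baseline controls as now, and with the outcome level in the interval ending at the mediator visit added. That is days of drug use for the drug-use outcome and days of buprenorphine for the adherence outcome. Report the two models side by side.

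State that the added covariate is post-randomisation. The adjusted estimate then excludes any mediation that already acted through early use and is conservative, so both models are to be read together as exploratory.

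The cost is a few sentences, one degree of freedom per model and a smaller estimated path. No new data are needed.

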## Discussion

The prevalence of OUD has reached epidemic rates in United States, and opioid-involved overdoses are now the country’s leading cause of injury deaths [50]. MOUD, including the use of buprenorphine, is effective at producing significant reductions in illicit opioid use as well as improvements in health-related outcomes (e.g., reduced risk of HIV) [6, 51]. However, despite the many advantages associated with buprenorphine treatment, nearly half of participants are unable to achieve stabilization [7], and many patients lapse or discontinue treatment in the initial weeks [8]. This is notable as early lapses are related to poor treatment prognosis and retention [8, 52]. Given high rates of noncompliance and/or discontinuation, there have been recent calls to find innovative interventions to enhance motivation, adherence, and retention in buprenorphine treatment [53].

Consistent with a negative reinforcement model of substance use, aversive internal states, that occur in the context of early periods of abstinence, may contribute to difficulties with buprenorphine stabilization [54]. Accordingly, an intervention that (a) cultivates motivation for abstinence over and above the reinforcing effects of opioids and (b) teaches adaptive strategies for tolerating physical and psychological discomfort may optimize stabilization on buprenorphine to improve the likelihood of long-term recovery. This Stage 1 behavioral treatment development trial seeks to develop, and pilot test, an innovative digital health intervention that aims to enhance motivation to engage in treatment and increase tolerance of distress to facilitate buprenorphine stabilization by providing skills training and motivational reminders in ‘real-time.’

At the conclusion of this study, our goals are to (1) evaluate the feasibility, acceptability, and preliminary efficacy of the iCOPE intervention components and (2) explore potential mechanisms underlying the effects of the intervention. Results of this study will be used to determine whether to proceed with further testing through a large-scale, fully-powered trial. Even if this study produces null effects of the proposed intervention, the data will still yield valuable information to inform future intervention development efforts.

This work has the potential to improve treatment outcomes by reducing illicit opioid use, increasing adherence/retention, and preventing future incidence of overdose. If successful, this study has high clinical and public health significance by developing and pilot testing the preliminary efficacy of an intervention that may reach a high-risk and vulnerable segment of the population. Further, by leveraging digital health platforms, this proposal has the potential for high scalability and impact.

## Data Availability

Not applicable.

## Abbreviations

OUD: Opioid use disorder
MOUD: Medications for opioid use disorder
DT: Distress tolerance
PFI: Personalized feedback intervention
TAU: Treatment-as-usual
DSM-5: Diagnostic and statistical manual of mental disorders, 5th Edition
RSC: Relative subjective count
AIC: Akaike information criterion
GEE: Generalized estimating equations
